### 2.5 Outcomes

In accordance with the different sets of hypotheses, the primary outcomes refer to the image-forming pathway enabling perception, and the non-image forming pathway responsible for non-image forming visual functions.

#### 2.5.1 Image-forming visual function.

The image-forming pathway is investigated using psychophysical tests, testing of contrast thresholds. During the tCS task, the contrast threshold is determined; contrast is measured in percent. We will average the contrast threshold block-wise across test repetitions, separate for each condition. A linear mixed model will be used to investigate hypotheses H2a to H2c. Our primary outcome variable is the point estimate for the temporal contrast sensitivity in each test for a specific post-receptoral mechanism and a specific frequency. The temporal contrast sensitivity is the inverse of the contrast threshold determined by a two-up-one-down staircase method.

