#### 2.4.4 In-laboratory visits.

During the forced-desynchrony session, participants will repeatedly undergo a battery of visual, physiological and psychometric tests during wakefulness. The experiments that will be administered during one repeatable block are described in Fig 3 and detailed below.

*Compliance during in-laboratory visit.* The experimenter will continuously monitor compliance and the successful completion of experiments. Given the demanding nature of the protocol, there is tolerance for participant’s failure to perform in individual tests. A block’s data is considered for analysis as long as one test repetition within that block is successful. However, experimentation will proceed across all modalities using light-emitting devices, even if data collection issues occur in a single modality. These devices serve a dual purpose: not only do they measure visual outcomes, but they also provide consistent light exposure > 10 lux, which is important for maintaining comparability between participants. If the experimenter fails to collect data from both primary modalities – pupillometry and psychophysics – for more than one block due to any reason (e.g., non-compliance, fatigue, tiredness), the experimental session may be aborted. This is because the increased measurement intervals would render the data unsuitable for testing circadian hypotheses.

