*Silent substitution of post-receptoral mechanisms.* We will probe the sensitivity for luminance and of the colour-opponent processes by means of (1) joint modulation of all three cones to target the luminance channel (L+M+S*), (2) isolated modulation of S-cones keeping the luminance channel constant (S*), and (3) antagonistic modulation of L- and M-cones to target the red-green channel (L–M*). The asterisk in condition labels indicates the lack of control over melanopic stimulation with the RGB monitor compared to the 6-LED stimulation device employed during pupillometry, e.g. S* is the S-cone isolating condition on the RGB monitor, where melanopsin activation cannot be kept at a constant level, while S is the S-cone isolating condition fixing L-, M-, and melanopsin-activation while modulating S activity. Maximum contrasts are predefined by the given colour gamut of the monitor (L+M+S*: 100%, S*: 51%, and L–M*: 6%) and starting values are partly lower as a trade-off between experiment length and visibility of the stimuli (L+M+S*: 90%, S*: 35%, and L–M*: 6%). The accidental activation of melanopsin will not be monitored. Effects of ipRGCs on the psychophysical tasks performance are assumed to be minimal.

*Post-receptoral temporal contrast sensitivity.* In the two-alternative forced choice (2AFC) tasks, stimulus contrast varies according to a staircase method, approaching the participant’s contrast threshold in relative steps. Contrast sensitivity is calculated from the threshold values. Within one test of the tCS task, different temporal frequencies, 2 and 8 Hz, are presented in interleaved order for one condition or photoreceptor mechanism. Participants determine whether the stimulus appears right or left from the centre of the screen with a left or right button press. Location varies randomly. After completion of three conditions, we will reiterate over the conditions twice, yielding nine tests per block. During the light exposure session (Sect 2.4.2), the participant will learn the task procedure, completing all 9 tests to achieve comparable light exposure levels. Tests are expected to last longer due to unfamiliarity in the light exposure session.

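### Section 2.5.1 gives two derivations of contrast sensitivity; in the block-wise one the value depends on how many tests succeed, and log sensitivity avoids the problem

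*Protocol article*

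**What the plan says.** Section 2.5.1 of the protocol article has thresholds measured in percent contrast and combined within blocks: "We will average the contrast threshold block-wise across test repetitions, separate for each condition". It then defines the primary outcome at another level: "Our primary outcome variable is the point estimate for the temporal contrast sensitivity in each test for a specific post-receptoral mechanism and a specific frequency". What links the two quantities is this definition: "The temporal contrast sensitivity is the inverse of the contrast threshold determined by a two-up-one-down staircase method". The kind of average is not named, and nothing says whether inversion comes before or after averaging.

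Section 2.4.6 sets the number of tests: "After completion of three conditions, we will reiterate over the conditions twice, yielding nine tests per block". That is three per condition, each covering both 2 Hz and 8 Hz. It describes the staircase as "approaching the participant’s contrast threshold in relative steps". Section 2.4.4 adds: "A block’s data is considered for analysis as long as one test repetition within that block is successful". It lists fatigue and tiredness among possible reasons for lost data.

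Section 2.6.2 puts sensitivity T into eqs (3) and (4), which have additive error, one error term and person-specific intercepts and sine and cosine weights. It mentions neither a log transform nor the number of tests behind each value.

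**The concern.** The order of averaging and inverting matters because the inverse is a convex function. The inverse of an average of k thresholds has an expectation that falls as k rises, and here k may be 1, 2 or 3. Two blocks with the same true sensitivity can then differ in expected T only because a test failed. If failures followed circadian phase, part of that difference would be read as rhythm.

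The scale is a second matter, on either reading of 2.5.1. A staircase in relative steps makes it plausible that threshold error is proportional to the threshold. On the 1/threshold scale, sensitive participants would then have larger rhythms and larger noise, while the model gives everyone one residual variance. That costs precision in the six H2 comparisons (three mechanisms at two frequencies), and section 2.1.3 caps the sample at twelve by resources.

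**Working it through.** The article gives no threshold variability, failure rate or power for H2, so there is no figure of its own to reproduce. Every SD and amplitude below is an assumption.

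**1. Tests per value.** Nine tests over three conditions (2.4.6) give 9/3 = 3 per condition and block. The minimum for a block to count is 1 (2.4.4). So k = 1, 2 or 3.

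**2. Dependence on k, block-wise reading.** Take lognormal repeat error with SD s on the ln scale, so CV² = exp(s²) − 1. To second order, E[1/mean of k] ≈ (1 + CV²/k)/E[threshold]; for k = 1 this is exact. The ratio of a one-test to a three-test block is (1 + CV²)/(1 + CV²/3).

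| Repeat SD, log10 | s (× 2.3026) | CV² | Ratio by formula | Simulated excess |
|---|---|---|---|---|
| 0.10 | 0.230 | 0.054 | 1.054/1.018 = 1.036 | 3.6% |
| 0.15 | 0.345 | 0.127 | 1.127/1.042 = 1.081 | 8.0% |
| 0.20 | 0.461 | 0.236 | 1.236/1.079 = 1.146 | 14.7% |

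Two tests against three matter less: 0.7%, 1.5%, 2.7% and 4.2% at ln SD 0.2, 0.3, 0.4 and 0.5.

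**3. Effect on the test for a rhythm.** No true rhythm, 12 participants, 11 blocks, 30% of tests failing, two-sided 0.05. The two tests were Hotelling's T² on per-person cosinor weights and a pooled within-person F test.

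| Failures | Outcome | False-positive rate |
|---|---|---|
| Random | 1/mean threshold | about 0.04 to 0.05 |
| Phase-linked (30% ± 25 points), ln SD 0.2–0.3 | 1/mean threshold | about 0.05 |
| Phase-linked, ln SD 0.4–0.5 | 1/mean threshold | about 0.065 to 0.085 |
| Phase-linked, ln SD 0.2–0.5 | mean log threshold | about 0.03 to 0.05 |

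**4. Effect of the scale.** Three tests in every block, 7% amplitude, Hotelling power, raw → log:

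| Repeat SD (ln) | Between-person SD 0 | 0.2 | 0.4 | 0.6 |
|---|---|---|---|---|
| 0.2 | 0.87 → 0.88 | 0.85 → 0.88 | 0.79 → 0.87 | 0.69 → 0.88 |
| 0.3 | 0.58 → 0.58 | 0.58 → 0.61 | 0.50 → 0.61 | 0.43 → 0.60 |

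A between-person SD of 0.15 log10 is 0.15 × 2.3026 = 0.345 on the ln scale, between the 0.2 and 0.4 columns. Linear interpolation gives a gain of about 3 + 0.725 × (8 − 3) = 6.6 points in the first row and 3 + 0.725 × (11 − 3) = 8.8 in the second. Inverting before or after averaging changes raw-scale power by about 3 points at most, so the loss comes from the scale and not from the order.

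**5. Closer to the plan's model.** Eq. (3) against eq. (4) by maximum likelihood with a BIC-approximated Bayes factor, ln repeat SD 0.2, 8% amplitude. The chance of exceeding 10, raw → log, was 0.60 → 0.61, 0.51 → 0.59, 0.49 → 0.61 and 0.49 → 0.67 at between-person SD 0, 0.2, 0.4 and 0.6. Each cell has 150 runs, so a single figure has a standard error of about √(0.5 × 0.5/150) = 0.04.

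**The case against.** The strongest reply is that the block-wise derivation is not settled. If each test's threshold is inverted and enters the model singly, the expectation does not depend on k. That is correct. It leaves the article with two incompatible units for a primary outcome, and the scale question is untouched.

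A second reply is that a condensed article may leave transformation and weighting to an analysis plan. That holds for a detail left open. Here the article states a derivation, and its sentences conflict.

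Three stronger readings are tempting, and the documents do not support them.

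- A reader might infer that sensitivity will rise at night by arithmetic alone. That needs failures concentrated in the night blocks across participants. The article gives no failure rate, does not say that failures cluster by phase, and in section 1.3 describes the nap schedule as holding sleep pressure constantly low.
- A reader might infer that eq. (4) forces one amplitude on everyone. It does not, since it has person-specific sine and cosine weights. Only the shared residual variance stands.
- A reader might infer a definite loss in the chance of reaching a Bayes factor above 10 for H2. Section 2.1.3 sets that threshold as a stopping rule on the melanopsin pupil model only. The figure also depends on the model. At repeat SD 0.15 and amplitude 0.03 log10, a BIC comparison with a common amplitude gives 0.20 raw against 0.31 log at between-person SD 0.15 log10. With eq. (4)'s random slopes both fall to the floor, 0.01 against 0.02.

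Relative steps describe how the staircase moves, not how its error is distributed. Unbounded lognormal error also ignores the monitor's ceiling, since the L–M* condition starts at its 6% maximum.

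**Conclusion.** The point holds in limited form. Section 2.5.1 contradicts itself on the unit of the H2 outcome and leaves the order of averaging and inverting open. On the block-wise reading with an arithmetic mean, dependence on the number of successful tests follows from convexity. Its size, about 3.6% to 14.7% for one test against three, rests on assumed repeat SDs of 0.10 to 0.20 log10. It biases the test for rhythm only with phase-linked failures and large repeat error.

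The scale loss is conditional on proportional error and rhythm: about 0 to 3 points of power when participants are alike, about 5 to 10 at a between-person SD of 0.15 log10, and more at wider spreads. None of these figures is the plan's own Bayes factor. This is a cheap improvement worth making before analysis, not a threat to the study.

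**What to change.** In 2.5.1, state one order of operations and one unit of analysis: for each block, condition and frequency, average the log10 thresholds of the successful tests and take minus that mean (log10 contrast sensitivity) as the outcome. Averaging log thresholds or log sensitivities gives the same value apart from sign, so the order no longer matters, and the expectation does not change with the number of tests.

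In 2.6.2, use this outcome as T in eqs (3) and (4). Weight by the number of successful tests, or let the residual variance depend on it (for example σ²/k), and report that number by block. Back-transform amplitudes to percent change.

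The cost is a sentence or two in each section and no new data. The one downside is that amplitudes are read as proportional change and not in units of inverse percent contrast.

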#### 2.1.3 Sample size.

This study will follow a within-person design. Each participant provides eleven repeated measurements. We will determine evidence for our hypotheses using a sequential Bayesian sampling strategy, such that data collection will continue until evidence strength suffices, or until a maximum of twelve participants. This maximum sample size is set by resource limitations. For the sequential sampling strategy, we will use Sequential Bayes Factor (BF) of the statistical model testing circadian modulation of melanopsin-dependent pupil constriction. The stopping criterion is BF > 10 or BF < 1/10 to quantify evidence strength for or against a circadian effect.

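### The psychophysics primary outcome is defined both as a block average and per test, with no block term in the model, and the staircase rule is named in a way that does not work on its usual reading

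*Protocol article*

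**What the plan says.** Section 2.5.1 describes the data reduction for the temporal contrast sensitivity task: "We will average the contrast threshold block-wise across test repetitions, separate for each condition". In the same paragraph it defines the outcome, for a given mechanism and frequency: "Our primary outcome variable is the point estimate for the temporal contrast sensitivity in each test". It then adds: "The temporal contrast sensitivity is the inverse of the contrast threshold determined by a two-up-one-down staircase method".

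Section 2.4.6 sets the number of tests: "After completion of three conditions, we will reiterate over the conditions twice, yielding nine tests per block". Within one test, "different temporal frequencies, 2 and 8 Hz, are presented in interleaved order for one condition or photoreceptor mechanism", so each test yields one threshold per frequency. The task is two-alternative forced choice.

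Section 2.1.3 says "Each participant provides eleven repeated measurements" and recruits "until a maximum of twelve participants" at most. Section 2.4.4 keeps a block in the analysis if at least one repetition in it succeeded. Section 2.6.2 applies equations (3) and (4) to temporal contrast sensitivity, separately for 2 Hz and 8 Hz. Their random terms are a participant intercept and, in the full model, participant-specific sine and cosine effects. Neither model has a term for the block.

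**The concern.** One paragraph gives the primary outcome for H2a–H2c two different units. An analyst could follow either sentence and build a dataset that differs threefold in rows.

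Tests in one wake period are likely to share sleepiness, adaptation and optical alignment. If they do, their residuals are correlated within the block. A model with only participant-level random effects counts each test as separate evidence about the rhythm, so chance differences between blocks look better supported than they are.

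Two smaller matters sit in the same paragraph. Thresholds are averaged but their inverse is the outcome, and the order of the two operations is not fixed. The named staircase rule, read in the usual way on contrast, aims at a performance level below guessing, so a reader cannot tell which performance level the threshold represents.

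**Working it through.** **Count of tests and rows**
- Tests per block: 3 conditions × (1 + 2 further passes) = 9, which reproduces the figure in section 2.4.6. Each condition therefore has 3 tests per block.
- Block definition: 11 values per person for each mechanism and frequency; 11 × 12 = 132 rows at the maximum sample.
- Per-test definition: 11 × 3 = 33 values per person; 33 × 12 = 396 rows, three times as many.

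**Effect of ignoring the block**

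Let r be the residual correlation between tests in one block. The protocol gives no value, so r is assumed. The three tests carry 3 / (1 + 2r) effective observations, and the variance is understated by 1 + 2r. The simulation had no rhythm, 12 people, 11 blocks 3.75 h apart, 3 tests per block, a period of 24.2 h and 2,000 runs. It used an F-test of common sine and cosine terms with participant intercepts, at nominal 5%.

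| Assumed r | 1 + 2r | Effective tests per block | Null rejection, per test | Null rejection, block means |
|---|---|---|---|---|
| 0 | 1.0 | 3.0 | 4.8% | 5.9% |
| 0.3 | 1.6 | 1.9 | 16.5% | 5.1% |
| 0.5 | 2.0 | 1.5 | 23.0% | 4.2% |
| 0.7 | 2.4 | 1.25 | 30.3% | 5.7% |

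This F-test shows direction and rough size. It is not the planned Bayes factor.

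**Order of averaging and inversion**

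For three lognormal thresholds with an assumed between-test CV of 10%, 20%, 30% or 50%, the mean of the inverses exceeds the inverse of the mean by about 1%, 3%, 6% or 15%.

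**Staircase**

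Let p be the probability of a correct response and q = 1 − p.
- Contrast raised after two errors and lowered after one correct response: up and down moves balance when q² = 0.5, so p = 1 − 0.707 = 29.3%. The guess rate is 50%. At pure guessing, up moves per trial are q²/(1 + q) = 0.25/1.5 = 1/6 and down moves are 1/2, a net fall of one third of a step per trial.
- A simulation of that rule (500 runs, assumed Weibull slope 3.5, step 0.05 log10 units) shows the drift. Mean log10 contrast relative to threshold was −0.46, −1.31, −2.97 and −6.36 after 50, 100, 200 and 400 trials. It does not settle.
- Harder after two correct, easier after one error: p² = 0.5, so p = 70.7%. In simulation it settles at about −0.09.
- Two steps up after an error, one step down after a correct response: p × 1 = (1 − p) × 2, so p = 66.7%. It also settles, at about −0.15.

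**The case against.** The strongest reply on the unit is that the protocol already leans to the block. Section 2.5.1 itself prescribes block-wise averaging, section 2.1.3 counts eleven measurements, section 2.4.4 retains data by block, and section 2.5.2 averages the pupil outcome over test repetitions. The per-test phrase may only name the raw estimate that is then averaged. This stands in large part. A reader might infer that the plan is to analyse single tests and will produce false evidence for H2a–H2c; the document does not support that. What remains is that the only sentence naming the primary outcome uses the other unit.

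On size, the planned inference is a Bayes factor and its prior is not stated. Null simulations of equations (3) and (4) with BIC-type approximations differing only in penalty put the per-test chance of a Bayes factor above 10 at 0–15% for r = 0.3 and 3–43% for r = 0.5. The direction holds, but no single percentage can be defended. Moreover, that threshold is stated only as the stopping criterion for the melanopsin pupil model.

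On the staircase, a reader might infer that it cannot converge and that the device is misconfigured. The document does not define up and down, and two other readings converge. A transposed name for a standard rule is the likeliest explanation, and a condensed article may leave the target percentage to the full protocol.

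On averaging order, if relative variability is constant over the session, the two versions differ by a constant factor in expectation. That rescales mean level and amplitude together and neither creates nor removes a rhythm.

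**Conclusion.** The contradiction in section 2.5.1 is real and should be resolved before the psychophysics data are modelled. The row count differs by exactly three. If per-test values were used with equations (3) and (4) as written, evidence for a rhythm would be overstated whenever r exceeds 0: a design effect of 1.6 or 2.0 at r of 0.3 or 0.5, and F-test null rejection of about 16% or 23% against 4–6% with block means. These figures rest on assumed correlations and on a stand-in test. At r = 0 there is no harm. The sequential stopping rule and the maximum of twelve use the pupil model only and are not touched.

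The averaging order is a reporting gap with little bearing on the test. The staircase is misnamed or undefined: wrong on its usual contrast reading, but not shown to be wrong in operation.

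**What to change.** 1. Define the modelled outcome as one value per block, mechanism and frequency, taken over the successful repetitions, and remove the per-test wording. Alternatively, keep per-test values and add a random block-within-person effect to both the null and the full model.
2. State whether sensitivity is the inverse of the mean threshold or the mean of the inverses. Averaging on the log scale is an option that makes the two agree; it is not required to resolve the contradiction.
3. Check the device setting and restate the staircase with its direction and target. An example is contrast lowered after two consecutive correct responses and raised after one incorrect response, targeting 70.7% correct, if that is what is run.

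The cost is a few sentences and one check of the device. The block-average route needs no change to the models or to data collection; the per-test route adds one variance component to each model.

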#### 2.5.2 Non-image-forming visual function.

For the non-image forming pathway, we test the PLR using pupillometry. There are various metrics to quantify pupil kinetics, but the maximum pupil constriction is particularly well-suited to capture the rapid photoreceptor responses of the cones. The primary outcome variable is the relative pupil constriction *R* in response to a receptor- or mechanism-isolating stimulus. To obtain a measure of relative pupil constriction, we will obtain a maximum pupil constriction amplitude per trial from the pupil trace. Maximum pupil constriction is defined by the maximum difference between pupil diameter one second prior to stimulus onset and the pupil diameter during the 5-second stimulus presentation. We will calculate the average pupil response amplitude across trials and test repetitions for each condition. The final outcome measure is calculated by normalising the average pupil response amplitude in response to a specific condition against the average response amplitude to the combined modulation of all cones and melanopsin at equal contrast “(Light flux stimulation)”, as specified in eq. (1).

$$R_{condition}=\frac{A_{condition}}{A_{all}}$$
(1)

We use the PLR to refer to the ratio *R* of response amplitudes. To investigate hypotheses H1a to H1d, we will use statistical modelling linear mixed effects as detailed in eq. (4).

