### 1.4 Hypotheses

Building upon prior evidence for a time-of day dependency in image-forming (i.e., luminance and colour perception) and non image-forming functions (i.e., pupillary light response), we hypothesize that photoreceptor sensitivity and retinal mechanisms are modulated by the circadian rhythm.

Our hypotheses regarding variations in non-image forming function investigate circadian effects in the pupillary light reflex to different conditions.

The detailed confirmatory hypotheses state that the PLR shows circadian effects in the response to

modulation of the colour opponent process L-M with constant activation of S and melanopsin (L–M) [H1a];modulation of the S-cones with constant activation of L-cone, M-cone, and melanopsin activation (S) [H1b];joint modulation of L-, M-, and S-cones (L+M+S) [H1c];selective modulation of melanopsin activation (Mel, constancy of cone activation) [H1d].

To investigate circadian effects isolated from homeostatic effects in the image-forming pathway by evaluating temporal contrast threshold to two different frequencies, focusing on the following photoreceptor mechanisms using silent-substitution stimuli: activation of the luminance channel (L+M+S), post-receptoral red-green channel (L–M), activation of the S-cones (S-(L+M)), activation of melanopsin-driven signaling in ipRGCs. We will evaluate the contrast sensitivity to:

modulation of the colour opponent process L-M with constant activation of S (L–M*) [H2a];modulation of the S-cones with constant activation of L-cones and M-cones (S*) [H2b];joint modulation of L-, M- and S-cones (L+M+S*) [H2c],

with none of the conditions controlling for melanopsin modulation, as indicated by the asterisk. The hypotheses regarding psychophysical performance in image-forming vision, relates to two different frequencies, yielding six different hypothesis: each hypothesis will be investigated for a low frequency (2 Hz) and a high frequency (8 Hz) to identify and possible explore differences based on temporal sensitivity.

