
*Silent substitution stimuli.* Spectral composition of the light stimuli is varied to achieve silent substitution of the photoreceptor mechanisms of interest. Briefly, this means the activity of one or more photoreceptors is selectively modulated while the activation of other photoreceptors is kept constant [13,46–48]. While rods are saturated photopic light levels [49,50], stimuli will modulate melanopsin and cone activation for five conditions: (1) joint modulation of all photoreceptors (Light flux, melanopsin-containing ipRGCs, L-, M-, and S-cones) (2) joint modulation of all cones while keeping melanopsin activity constant (L+M+S) (3) selective modulation of melanopsin activation (Mel, constant of L, M, S activation) (4) selective modulation of S-cone activation (S) (5) selective modulation of the red-green colour channel activity (L–M). Comparing the four listed conditions against the Light flux condition, we will determine the unique circadian variation of the photoreceptor mechanisms.

The action spectra we used for the calculation of the silent substitution spectra stem from the default settings of the *PySilSub* package: the cone fundamentals of the macula from [58], and the melanopic and rhodopic action spectra [59] for a 32-year-old standard observer. We did not perform an age-adjustment considering different lens transmittance, when calculating the silent substitution spectra. We will simulate the response and report the residual variation, or deviation between obtained and target contrast, in the contrast of retinal mechanisms and photoreceptors after silencing. We will disclose the effective precision of photoreceptor by calculating the so-called *contrast splatter* using the same method as [13].

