*Experimental procedure.* During the forced-desynchrony session, every participant then completes 11 blocks, with a test and a test repetition in each block. Each test encompasses an adaptation period and 25 trials. Participants adapt to a photopic background ($60\;{cd/m}^{2}$) for four minutes, to ensure rod saturation. The adaptation period is followed by 25 trials per test, where participants will view sinusoidal light modulations with a frequency of 0.4 Hz, interspersed with white baseline stimulation. 0.4 Hz was selected to measure pupil responses in a temporal regime in which all photoreceptors are likely responsive [13]. The experimental stimulus presentation takes place for five seconds, followed by a period of baseline stimulation with white light of 13 seconds, yields a total trial duration of 17 seconds. One test consists of 25 trials, five repetitions of each experimental condition; conditions are counterbalanced using an m-sequence. One test takes about 12–15 minutes, amounting to about 30 minutes per block for pupillometric assessment. A short break temporally separates the two tests.

*Control for rod intrusion.* As recent literature as shown that rods phototransduction may recover even at high light levels and based on temporal modulation [50,51], we will conduct a control experiment to test whether rods escape saturation. The control experiment will take place after data collection of the main study has been completed and will include a different set of participants than the participants in the main trial. Using pupillometry, we will evaluate the response to silent substitution stimuli targeting rods at light levels comparable to the planned experimental condition and with the same temporal frequencies. The results of this control study will be reported and discussed in the context of the results seen in the main study in subsequent publications.

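### The pupil outcome R measures circadian variation only relative to Light flux, so it cannot carry the absolute conclusions drawn from H1a–H1d and the stopping rule

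*Protocol article*

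**What the plan says.** All references are to the protocol article.

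- **Hypotheses (Section 1.4).** The general statement is absolute: "we hypothesize that photoreceptor sensitivity and retinal mechanisms are modulated by the circadian rhythm". The specific one reads "The detailed confirmatory hypotheses state that the PLR shows circadian effects in the response to" each of four modulations: L–M, S, L+M+S and melanopsin.
- **Outcome (Section 2.5.2).** The amplitude for each condition is normalised "against the average response amplitude to the combined modulation of all cones and melanopsin", which is eq. (1), R = A_condition/A_all. The section adds: "We use the PLR to refer to the ratio *R* of response amplitudes".
- **Denominator (Section 2.4.5).** Light flux is the "joint modulation of all photoreceptors (Light flux, melanopsin-containing ipRGCs, L-, M-, and S-cones"), so it contains every mechanism named in H1.
- **Purpose (Section 2.4.5).** "Comparing the four listed conditions against the Light flux condition, we will determine the unique circadian variation of the photoreceptor mechanisms".
- **Averaging.** Section 2.5.2 takes the "average pupil response amplitude across trials and test repetitions for each condition", and in Section 2.4.5 "every participant then completes 11 blocks, with a test and a test repetition in each block".
- **Test (Section 2.6.2).** R over time is compared, by Bayes factor, with a model in which it is constant.
- **Stopping (Section 2.1.3).** Recruitment stops, up to a maximum of 12 participants, when the Bayes factor for circadian modulation of melanopsin-dependent constriction exceeds 10 or falls below 1/10. That result is read as evidence for or against a circadian effect.

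Neither the confirmatory section (2.6.2) nor the exploratory section (2.6.3) names a test of A_all or of the un-normalised A_condition.

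**The concern.** A ratio isolates its numerator only if its denominator is steady. Here the denominator is built from the mechanisms that the study expects to vary with circadian phase, so the general hypothesis itself gives reason to expect that A_all is not flat. Section 1.1 raises a circadian gating of the retinal signal. If such gating scaled all responses alike, R would not show it.

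Two wrong readings become possible:

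- A Bayes factor below 1/10 on R could be reported as evidence against modulation although the response itself is rhythmic.
- A Bayes factor above 10 for a cone condition could come only from a rhythm in the denominator. The amplitude and phase from eqs (5)–(6) would then be assigned to the wrong mechanism.

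All four H1 tests share this denominator, so they can be affected together. Section 2.6.2 gives no other pupil model than the one for R, so the stopping rule is exposed as well.

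**Working it through.** **Inputs.** From the article: eq. (1), 11 blocks, 2 tests per block and 5 trials per condition per test (2 × 5 = 10 trials per condition per block), at most 12 participants, and thresholds of 10 and 1/10. The article gives no circadian amplitude, noise level, melanopsin share of A_all or prior, so those below are assumptions. It states no power or effect size for R, so there is no figure to reproduce.

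**Reading of A_all.** Amplitudes are averaged over the trials and two tests of a block, and R is modelled as a function of time. I therefore read A_all as specific to each block.

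**Algebra.** Let A_condition = M_c[1 + k_c cos(ωt − φ_c)] and A_all = M_a[1 + k_a cos(ωt − φ_a)]. To first order the relative rhythm in R is

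k_c cos(ωt − φ_c) − k_a cos(ωt − φ_a).

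The exact first harmonic of the ratio over 24 h, for assumed amplitudes, is:

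| Condition | Light flux | Rhythm seen in R |
|---|---|---|
| 10% | 10%, same phase | 0% |
| 0% | 10% | 10%, antiphase |
| 10% | 0% | 10% |
| 10% | 5%, same phase | 5% |
| 5% | 10%, same phase | 5%, phase reversed |
| 10% | 10%, 6 h apart | 14%, phase shifted |

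**Rhythm in melanopsin only.** Assume a 20% rhythm and a linear sum, with melanopsin supplying a share m of A_all. Then A_all = 1 + x cos(ωt) with x = 0.2m. Taking (max − min)/(max + min) of each ratio:

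- a cone condition with no rhythm, 1/A_all, shows x, in antiphase;
- melanopsin, (1 + 0.2 cos ωt)/A_all, shows (0.2 − x)/(1 − 0.2x).

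| m | x = spurious cone rhythm | Melanopsin rhythm left in R |
|---|---|---|
| 5% | 0.01 (1%) | 0.19/0.998 = 19% |
| 20% | 0.04 (4%) | 0.16/0.992 = 16% |
| 30% | 0.06 (6%) | 0.14/0.988 = 14% |
| 50% | 0.10 (10%) | 0.10/0.980 = 10% |

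**Effect on the Bayes factor (illustration).** The simulation used 12 participants × 11 blocks and 2000 runs per scenario, a fixed 24 h period, a unit-information g-prior in place of the unstated priors, and no random slopes. Block-level CVs for numerator, denominator and shared noise were 10%, 5% and 5% (lower noise) or 20%, 10% and 10% (higher noise). Results are lower / higher noise.

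| Rhythm: condition, Light flux | R: BF > 10 | R: BF < 1/10 | Un-normalised: BF > 10 | Un-normalised: BF < 1/10 |
|---|---|---|---|---|
| 10%, 10% | 0% / 0.2% | 93.2% / 92.5% | 100% / 49.2% | 0% / 6.1% |
| 0%, 10% | 100% / 47.4% | 0% / 6.6% | 0% / 0.1% | 92.4% / 91.4% |
| 10%, 5% | 48.0% / 2.8% | 5.2% / 58.0% | 100% / 48.2% | 0% / 6.6% |
| 0%, 0% | 0.1% / 0% | 92.1% / 92.7% | 0.1% / 0.3% | 92.6% / 92.7% |

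For R, the first row is practically indistinguishable from the last, where nothing is rhythmic.

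**The case against.** The best defence is that the relative comparison is deliberate. Section 2.5.2 defines the PLR as R, H1 is worded about the PLR, and Section 2.4.5 says why conditions are compared with Light flux. A reader might infer that R does not test H1a–H1d at all. The documents do not support that: by their own definition R tests H1 in a relative form, and removing variation common to all conditions is partly intended. Normalising also protects against arousal and noise that affect every condition. This part of the defence stands.

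It does not cover the conclusions. The general hypothesis and the stopping rule speak of mechanisms being modulated, without reference to Light flux. Nor does R deliver variation unique to one mechanism, because a rhythm in another mechanism also moves it. R cannot tell shared noise from a shared circadian signal.

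It is also fair to say that the sizes are not documented. Section 2.5.2 describes the metric as well suited to cone responses, so a small melanopsin share, with an effect near 1%, cannot be excluded. Finally, Light flux is recorded in every block and Section 2.6.3 allows further analyses, so nothing prevents a test of A_all. But such a test would not by itself change what the confirmatory Bayes factor is taken to mean, or when recruitment stops.

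**Conclusion.** The point holds in this form: R tests whether a condition's circadian variation differs from that of Light flux. Neither a Bayes factor above 10 nor one below 1/10 on R can be attributed to the named mechanism unless A_all is flat. The direction follows from eq. (1) and the composition of Light flux, given that A_all is computed per block.

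The size is conditional. For a 20% rhythm confined to melanopsin and a linear sum, it runs from about 1% spurious cone rhythm with 19% left for melanopsin (5% share) to about 10% and 10% (50% share). The simulated percentages show how the error can act on the decision thresholds. They rest on assumed noise and a stand-in prior and are not this trial's operating characteristics.

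A reader might also infer that Light flux carries the same rhythm as each condition, so that R must be flat. No section says so. Full cancellation needs equal relative amplitude and phase; otherwise the rhythm is attenuated, enlarged, shifted or reversed.

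**What to change.** 1. Keep R as the mechanism-specific measure.
2. Fit eqs (3)–(4) also to the un-normalised A_condition for each of the four conditions, and to A_all itself. A_condition divided by a per-person mean of A_all that is constant over time would serve equally. If such a constant was always intended in eq. (1), one sentence saying so settles the matter. Dividing by the pre-stimulus diameter of each block would not be a safe substitute, because that denominator may be rhythmic too.
3. Attribute a rhythm to a named mechanism only when the un-normalised amplitude and R agree. Do not read a Bayes factor below 1/10 on R as evidence against modulation unless A_all is also flat.
4. Either base the stopping Bayes factor on the un-normalised melanopsin amplitude, or restate H1a–H1d and the stopping rule explicitly as relative to Light flux. Settle this before sequential Bayes factors are read.

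The cost is some wording and a few more model fits on measurements already in the protocol. The drawback is that the un-normalised amplitude is less protected against arousal effects common to all conditions, which is why both measures should be reported.
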